## Abstract

**Background:**

Many patients with metastatic breast cancer experience cancer- and treatment-related side effects that impair activities of daily living and negatively affect the quality of life. There is a need for interventions that improve quality of life by alleviating fatigue and other side effects during palliative cancer treatment. Beneficial effects of exercise have been observed in the curative setting, but, to date, comparable evidence in patients with metastatic breast cancer is lacking. The aim of this study is to assess the effects of a structured and individualized 9-month exercise intervention in patients with metastatic breast cancer on quality of life, fatigue, and other cancer- and treatment-related side effects.

**Methods:**

The EFFECT study is a multinational, randomized controlled trial including 350 patients with metastatic breast cancer. Participants are randomly allocated (1:1) to an exercise or control group. The exercise group participates in a 9-month multimodal exercise program, starting with a 6-month period where participants exercise twice a week under the supervision of an exercise professional. After completing this 6-month period, one supervised session is replaced by one unsupervised session for 3 months. In addition, participants are instructed to be physically active for ≥30 min/day on all remaining days of the week, while being supported by an activity tracker and exercise app. Participants allocated to the control group receive standard medical care, general written physical activity advice, and an activity tracker, but no structured exercise program. The primary outcomes are quality of life (EORTC QLQ-C30, summary score) and fatigue (EORTC QLQ-FA12), assessed at baseline, 3, 6 (primary endpoint), and 9 months post-baseline. Secondary outcomes include physical fitness, physical performance, physical activity, anxiety, depression, pain, sleep problems, anthropometric data, body composition, and blood markers. Exploratory outcomes include quality of working life, muscle thickness, urinary incontinence, disease progression, and survival. Additionally, the cost-effectiveness of the exercise program is assessed. Adherence and safety are monitored throughout the intervention period.

**Discussion:**

This large randomized controlled trial will provide evidence regarding the (cost-) effectiveness of exercise during treatment of metastatic breast cancer. If proven (cost-)effective, exercise should be offered to patients with metastatic breast cancer as part of standard care.

**Trial registration:**

ClinicalTrials.govNCT04120298. Registered on October 9, 2019.

**Supplementary Information:**

The online version contains supplementary material available at 10.1186/s13063-022-06556-7.

## Background

Breast cancer is the most commonly diagnosed cancer and the leading cause of cancer mortality among women worldwide [1]. The majority of breast cancer-related deaths are due to metastatic breast cancer (mBC) [2]. Despite the availability of a number of treatment options, treatment of mBC remains palliative with a poor median 5-year survival rate of 25% [3]. Hence, maintaining the quality of life (QoL) is one of the most important goals for patients with mBC. Side effects that affect patients’ QoL include fatigue, decreased physical fitness, insomnia, depression, neuropathy, and pain [4–8]. Of these side effects, fatigue has the most substantial impact on QoL by negatively affecting activities of daily life. Therefore, interventions that can improve QoL by alleviating fatigue and other cancer- and treatment-related side effects during palliative treatment are needed.

There is ample evidence that exercise is safe and well-tolerated during and after curative cancer treatment, and that it has a significant, positive effect on a range of side effects, including fatigue [9]. To date, these positive effects of exercise have not been demonstrated in patients with mBC, since these patients are typically excluded from exercise interventions due to the potential risk of bone fractures and poor prognosis. Only very few, mainly small studies with short interventions have been performed. A recent systematic review in patients with advanced cancer, including patients with mBC, showed that exercise is safe and feasible [10]. More specifically, it has been shown that exercise appears safe in patients with bone metastases, if it includes a supervised component [11]. The summarized evidence indicates that exercise improves physical performance and functioning in patients with advanced cancer, whereas the effects on fatigue, QoL, and other cancer- and treatment-related side effects are mixed [10]. A high-quality and adequately powered study is needed to evaluate comprehensively the efficacy of exercise in patients with mBC.

The randomized controlled EFFECT study is designed to assess the effects of a structured and individualized 9-month exercise intervention in patients with mBC on QoL and physical fatigue. Secondary aims are to investigate the cost-effectiveness of the exercise intervention and exercise effects on other cancer- and treatment-related side effects and blood markers. We also investigate the effects of exercise on overall survival, breast cancer-specific survival, and progression-free survival. Here, we describe the design of the EFFECT study.

## Methods/design

### Study design

The EFFECT study is a multinational, randomized controlled trial with two study arms: 1) the intervention arm that receives a 9-month structured and individualized exercise program in addition to usual care, and 2) the control arm that receives general physical activity advice and an activity tracker in addition to usual care, but no structured exercise program.

The study protocol was approved in October 2019 by the institutional review board of the University Medical Center Utrecht, the Netherlands, and by the local ethical review boards of all participating institutions. Written informed consent will be obtained from all participants. The study was registered with ClinicalTrials.gov on October 9, 2019 (*NCT04120298*). The first patient was included on January 8, 2020.

More information about organizational aspects of the trial can be found in Appendix I.

### Study population

We plan to include a total of 350 patients with mBC, both male and female. Patients must meet the following inclusion criteria: age ≥ 18 years; diagnosis of breast cancer stage IV; ECOG (Eastern Cooperative Oncology Group) performance status ≤ 2; and able and willing to perform the exercise program and wear the activity tracker. A patient who meets any of the following criteria is excluded from participation: unstable bone metastases inducing skeletal fragility; untreated symptomatic brain metastasis; estimated life expectancy <6 months; serious active infection; too physically active (i.e., >210 min/week of moderate-to-vigorous exercise) or already engaging in intense exercise training comparable to the EFFECT exercise program; severe neurologic or cardiac impairment according to the American College of Sports Medicine (ACSM) criteria [12]; uncontrolled severe respiratory insufficiency or being dependent on oxygen supplementation in rest or during exercise; uncontrolled severe pain; any other contraindications for exercise; any circumstances that would impede adherence to study requirements or ability to give informed consent; or pregnancy. Medical in- and exclusion criteria are checked by an involved physician at the treating hospital.

### Recruitment and randomization

Participants are recruited in Germany (Heidelberg University Hospital/German Cancer Research Center (DKFZ)/National Center for Tumor Diseases (NCT) Heidelberg and German Sport University Cologne (DSHS)), the Netherlands (University Medical Center Utrecht (UMCU) and the Netherlands Cancer Institute (NKI)), Poland (Wielkopolskie Centrum Onkologii (WCO)), Spain (Onkologikoa (ONK)), Sweden (Karolinska Institutet (KI)), and Australia (Australian Catholic University (ACU)). Some centers have invited additional recruitment sites to contribute patients to the study. The study procedures are summarized in Fig. 1. Potentially eligible patients are informed about the study by an oncology nurse or medical specialist during a regular visit or by mail/letter. In addition, social media (e.g., of national/local patient organizations) are used to recruit patients. Interested patients receive an informational letter explaining the study aims and procedures. After 1 week, the patient is approached by telephone to provide further information, answer questions and check the (remaining) in- and exclusion criteria. Eligible patients who are willing to participate are invited to the study center to sign written informed consent and to undergo baseline measurements. Patients who choose not to participate in the EFFECT study are asked, but not required, to provide a reason for non-participation.

**Fig. 1 Fig1:**
[figure not shown]
Recruitment and study procedures

After baseline assessments, participants are randomly allocated (1:1) to either the exercise intervention or control group by central computerized randomization using a blocked computer-generated sequence, effectively blinding randomization. Randomization is stratified by study center and therapy line (maximum of two treatments received versus more). Due to the nature of the intervention, blinding of participants, local study nurses, or investigators to intervention assignment is not possible.

### Exercise intervention

The 9-month exercise program starts with a 6-month period where patients participate in a supervised, multimodal exercise program of 1 h twice a week. Thereafter, one supervised session is replaced by one unsupervised session for 3 months. Supervision is performed by an exercise professional (trainer). This can be an exercise physiologist or (oncology) physiotherapist who is trained by the study team to ensure a safe and standardized execution of the exercise program. Exercise sessions are offered at community or hospital-based fitness centers, physical therapy practices, gyms or personal training facilities throughout the catchment areas of the recruiting sites and close to the patients’ home address.

Each participant has an intake session in order to individualize the standard exercise prescription to their specific needs. The multimodal exercise program comprises aerobic-, resistance- and balance components. In case of physical limitations, an adapted exercise program is provided. Questions of local trainers can be presented to the EFFECT exercise expert board (including oncologists and exercise professionals from all study centers).

If training facilities are closed due to local COVID-19 regulations or if participants do not feel safe to visit them, an alternative live-online training program is provided by the trainer that includes the same components as the face-to-face exercise program. If needed, the study team provides participants with the required training equipment (e.g., resistance bands and free weights for resistance training; a cycle ergometer or an aerobic step for aerobic training). Prior to the start of the live-online program, the trainer conducts one individual face-to-face exercise session in which the exercises, training equipment, and training documentation are explained. During each session, the trainer closely monitors each participant to ensure that all exercises are performed correctly and safely.

#### Balance training

Each exercise session starts with 5 min of balance training. The balance exercise component includes exercises involving a variety of different stances (e.g., tandem stand) and can be progressed by including more challenging tasks. Progression depends on the subjective evaluation of both the trainer and participant.

#### Aerobic training

The aerobic training consists of a moderate-intensity continuous training (MICT) and progresses to high-intensity interval training (HIIT). The aerobic training protocol is individualized based on the patient’s fitness level using the Maximal Short Exercise Capacity (MSEC) and estimated W_peak_ as determined at baseline, 3 and 6 months post-baseline with the Steep Ramp Test (SRT; *see Study Outcomes*). Since the prescribed training load applies to the cycle ergometer, at least one training session per week should be performed on a cycle ergometer. The other training session can be performed on the rowing machine, treadmill, or elliptical/cross trainer, using the Borg scale to monitor intensity. For participants with bone metastases, aerobic training is preferably performed on the cycle ergometer or treadmill.

The exercise intensity is gradually increased during the exercise program (Table 1). The perceived intensity of the aerobic training is assessed using the Borg scale [13]. Since this is a vulnerable population and health status can deteriorate, the load should be decreased by 10% if the Rate of Perceived Exertion (RPE; 6-20) is higher than 15, whereas the load can be increased by 10% if the RPE is lower than 13.

**Table 1 Tab1:** EFFECT exercise protocol

Week	Aerobic training (15 min)	Resistance training (35 min)
1–3	15 min MICT at 50–60% of W_peak_	Six exercises. Three sets per exercise^b^. The intensity is periodized, alternating between 10 and 12 reps with 70–75% of h1RM and 6 and 8 reps with 80–85% of h1RM every month.
4–14	Interval training^a^: 8 × 1 min at W_peak_, alternated with 1 min active rest at 30 Watts	
15–25	Interval training^a^: 3 × 3 min at 70% of W_peak_, alternated with 2 min active rest at 30 Watts	
26–36	Interval training^a^: 8 × 30 s at 65% of MSEC, alternated with 1 min active rest at 30% of MSEC	

*MICT* Moderate-Intensity Continuous Training, *MSEC* Maximal Short Exercise Capacity, *h1RM* hypothetical 1- Repetition Maximum

^a^All interval sessions start with a 3-minute warm-up at 30 Watts and conclude with a 3-minute cool-down

^b^Main exercises include the leg press, leg curl, leg extension, chest press, seated row, lat pulldown. Variations of these exercises are allowed and depend on the exercise modality

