#### Resistance training

Resistance training consists of six exercises targeting the major lower and upper body muscle groups. The exercises can be delivered using the following modalities: machine-based, free-weights, or body-weight. All resistance exercises are individualized based on the patient’s fitness level, which is assessed by the trainer during the intake session using 12-repetition maximum (12-RM) muscle strength tests. Three sets per exercise are performed and the intensity is periodized (Table 1). To ensure a sufficient training load throughout the 9-month intervention period, the weights are continuously adjusted according to a progressive training protocol and in line with the periodization (if the participant’s health status permits) so that the predefined maximum number of repetitions is met as closely as possible. For participants with bone metastases, 12-RM testing is not performed for exercises that load regions with bone metastases (Table 2). Accordingly, adaptations to resistance exercises are shown in Table 2.

**Table 2 Tab2:** Adaptations to the prescribed exercise program based on location of bone metastases

Metastases site	Resistance exercise^**a**^			Aerobic exercise		Flexibility
	Upper	Trunk	Lower	WB	NWB	Static
**Pelvis**	**√**	**√**	**√**^c^		**√**	**√**
**Axial skeleton (lumbar)**	**√**		**√**		**√**	**√**^d^
**Axial Skeleton (thoracic/ribs)**	**√**^b^		**√**	**√**	**√**	**√**^d^
**Proximal humerus**		**√**^b^	**√**	**√**	**√**	**√**^b^
**Proximal femur**	**√**	**√**	**√**^c^		**√**	**√**
**All regions**	**√**^b^		**√**^c^		**√**	**√**^d^

This table is adapted from Galvão et al. (2011) [14]

^a^Resistance exercises that load the affected region can be either omitted according this table or can be performed using a “start low, go slow” approach, depending on patient characteristics and the experience of the involved trainer. According to this approach, participants with bone metastases should start with low weights and more repetitions and increase weights gradually over time up to 10-12 repetitions if possible. Higher intensities (i.e., 6–8 repetitions with 80–85% of h1RM) should be avoided. Weights will be reduced if participants report pain during a resistance exercise or experience an increase in pain or pain medication since the last exercise session

√ = Target exercise region

^b^exclusion of shoulder flexion/extension/abduction/adduction and inclusion of elbow flexion/extension

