^c^exclusion of hip extension/flexion and inclusion of knee extension/flexion

^d^exclusion of spine/flexion/extension/rotation

*WB* weight bearing (e.g., walking), *NWB* non-weight bearing (e.g., cycling)

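### The aerobic text prefers the treadmill for any bone metastasis, but Table 2 leaves weight-bearing aerobic exercise unticked for pelvis, lumbar spine, proximal femur and all regions

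*Protocol article*

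**What the plan says.** The Aerobic training section sets a rule for everyone and then a preference for participants with bone metastases. For everyone, "at least one training session per week should be performed on a cycle ergometer", and "The other training session can be performed on the rowing machine, treadmill, or elliptical/cross trainer". For participants with bone metastases it adds: "For participants with bone metastases, aerobic training is preferably performed on the cycle ergometer or treadmill". The only table cited in that section is Table 1.

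Table 2 is printed under Resistance training, but its title covers the whole program: "Adaptations to the prescribed exercise program based on location of bone metastases". Besides resistance and flexibility columns it has two aerobic columns, WB and NWB. The legend explains WB as "weight bearing (e.g., walking" and gives cycling as the example of NWB. The key describes a tick as marking a target exercise region and does not say what an empty cell means.

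The running text sends the reader to Table 2 twice, both times about resistance work: "12-RM testing is not performed for exercises that load regions with bone metastases (Table 2" and "Accordingly, adaptations to resistance exercises are shown in Table 2". Footnote a, which allows a cautious start instead of omission, is attached to the resistance heading and speaks only of resistance exercises.

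**The concern.** Both statements are printed in the same article and address the same decision: which aerobic machine to use for a participant with bone metastases. The sentence gives one answer for all sites, and the table gives an answer that depends on the site. A trainer who follows the sentence to the letter could put a participant with a pelvic, lumbar or proximal-femur metastasis on the treadmill, a mode the table does not target there. Nothing in the aerobic text would send that trainer to the table.

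What is at stake is safe and uniform delivery of the intervention. The Discussion notes that the skeleton is the commonest distant site in breast cancer and refers to an expected increase in skeletal events, including pathological fracture. Aerobic work progresses to high-intensity intervals, and sessions are held in community gyms and practices as well as hospitals, at centers in six countries. A site-specific rule in such a setting should read the same wherever it appears.

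**Working it through.** No sample size, power or alpha figure bears on this point, so the check is a side-by-side reading.

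**Step 1: classify the two machines.** Table 2's legend gives walking as its example of weight-bearing exercise and cycling as its example of non-weight-bearing exercise. The treadmill is not classified by name. I take it as weight-bearing because walking is the article's own example.

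**Step 2: read the aerobic columns.** Each row of Table 2 has six cells in header order (upper, trunk, lower, WB, NWB, static), and the WB column contains both ticks and blanks. The blanks are therefore not a fault of text extraction.

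| Table 2 row | WB | NWB | Does the table support the treadmill preference? |
|---|---|---|---|
| Pelvis | blank | tick | no |
| Axial skeleton, lumbar | blank | tick | no |
| Axial skeleton, thoracic/ribs | tick | tick | yes |
| Proximal humerus | tick | tick | yes |
| Proximal femur | blank | tick | no |
| All regions | blank | tick | no |

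WB is ticked in 2 of 6 rows and blank in 4 of 6, that is, 3 of the 5 single sites plus the all-regions row. NWB is ticked in 6 of 6.

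**Step 3: compare with the sentence.** The cycle ergometer agrees with the table in every row. The treadmill agrees in 2 rows and lacks support in 4.

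**Step 4: look for anything that narrows the sentence by site.** The aerobic section has no such limit and no pointer to Table 2. Footnote a does not reach the aerobic columns. The adapted program for physical limitations, the expert board and the trainer instructions are described only in general terms, and none of these descriptions limits the treadmill by site.

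**Step 5: can the exposure be sized?** Under the cycling rule, the treadmill can occupy at most one of the two weekly sessions. Going further to a figure in minutes does not work, for two reasons.

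- Table 1's column heading reads "Aerobic training (15 min", but its entries do not add up to that. Counting 7 or 8 rests for eight bouts, 2 or 3 rests for three bouts, and the 3 + 3 minutes of warm-up and cool-down:
  - weeks 4–14: 8×1 + (7 or 8)×1 + 6 = 21 or 22 min
  - weeks 15–25: 3×3 + (2 or 3)×2 + 6 = 19 or 21 min
  - weeks 26–36: 8×0.5 + (7 or 8)×1 + 6 = 17 or 18 min

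  A total built on 15 minutes per session would not be an upper bound.
- In the last 3 months one session becomes an app-supported session, with exercises that can be done at home using body weight, free weights or resistance bands. If the remaining supervised session meets the cycling rule, no supervised treadmill time is left. A larger figure would need the home session to be the cycling session, which the description does not support.

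The number of participants with the affected sites is not stated either. I therefore give no exposure figure.

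**The case against.** The strongest reply is that the two statements can be reconciled. The sentence says preferably and offers two modes, so a trainer who chooses the cycle always complies with both. The preceding sentence lists rowing machine, treadmill and elliptical, so the bone-metastasis sentence can be read as steering away from the rowing machine and elliptical, with Table 2 then refining the choice by site. The article condenses a fuller protocol. Its Discussion says that all trainers receive specific instructions on bone-metastasis adaptations, and those instructions are not shown. Unstable bone metastases are excluded, each participant has an individual intake session, and trainers can consult an expert board. All exercise-arm participants are also encouraged to be active for at least 30 minutes on the remaining days, with no site restriction stated.

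Most of this stands, and it keeps the point small. A reader might infer that the protocol forbids treadmill exercise for these sites in one place and prescribes it in another, or that participants are being directed to unsafe exercise. The article supports neither reading. An empty cell is not declared a ban, the sentence does not require the treadmill at any site, and no risk figure is given.

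The reply does not remove the mismatch itself. This is not detail left to another document, since both statements are printed here. Footnote a shows that the table is used to decide omissions, at least for resistance work, so its blanks are not empty of meaning. For the second weekly session, the sentence leaves the treadmill as the only preferred alternative to cycling. The expert board answers questions, but a trainer who sees no conflict will not ask one.

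**Conclusion.** The point holds as a minor internal inconsistency with a patient-safety bearing. The text's preference for the treadmill is unrestricted, while the article's own site table does not support weight-bearing aerobic exercise in 4 of 6 rows. This rests on two readings: that treadmill exercise counts as weight-bearing, and that a blank cell means at least not targeted.

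The practical effect is confined to the choice of machine in at most one of two weekly sessions, for an unknown number of participants, and it may be nil if the trainer instructions already limit the treadmill by site. Randomization, endpoints, the significance level and power are unaffected. Confidence is high that the two statements differ and moderate that the difference matters in delivery.

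**What to change.** Amend the bone-metastasis sentence under Aerobic training so that it reads, in substance: *preferably on the cycle ergometer, or on the treadmill where Table 2 ticks weight-bearing exercise for the affected site(s)*. Extend the pointer to Table 2, which now covers resistance adaptations only, to aerobic exercise. Check that the instructions given to trainers say the same.

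The cost is one clause, one wider cross-reference and one document check, with no new data. Participants with pelvic, lumbar or proximal-femur metastases would have slightly less choice of mode in one weekly session. Cycling stays open for every site, so no aerobic training need be lost. If the wording counts as a protocol change, it may need ethics committee approval, as the COVID-19 changes did.
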